#### Recurrent stroke prediction

##### Sample size

For this study, a prediction model containing a maximum of six predictors will be developed for recurrent stroke. Therefore, at least 60 patients with a recurrent stroke are needed according to statistical guidelines.^35^ Ischemic stroke is estimated to recur in approximately 10% of the included patients.^36^ When accounting for a loss to follow-up rate of 10%, the required sample size will be approximately 650. Based on a historical stroke cohort (Dutch Acute Stroke Study: 2009–2013, METC number 08–373), we expect a participation rate of 90%.^37^ Thus, a minimum of 720 patients need to be asked for study participation. In a period of 36 months, at least 720 patients with suspected ischemic stroke will visit the Amsterdam UMC—location AMC, the St. Antonius hospital—location Nieuwegein and the UMC Utrecht.

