##### Model derivation

Complete case analysis will be performed as we expect only few missing values. A multivariable model containing all candidate predictors will be developed. The best predictive variables will be selected with backward selection. Akaike’s information criterion will be used to determine the best model fit. Hazard ratios and 95% confidence intervals will be calculated with Cox proportional hazards models. The proportionality hazards assumption will be checked by visual inspection of the Schoenfeld residual plots. The performance of the final model will be evaluated with measures of discrimination and calibration. Discrimination will be assessed with ROC curves and c-statistics. Calibration will be assessed with calibration plots.

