## Discussion

CTP has good sensitivity (80%) and specificity (95%) for brain infarct detection.^10^,^11^ However, accurate detection of small volume infarcts is still difficult with CTP because of noise and limited spatial resolution.^38^ In addition, evaluation of the posterior fossa is often hampered by streak artefacts.^39^ In case no stroke is visualized with CT, an MRI is sometimes indicated to ascertain the diagnosis. By improving the detection of small volume stroke by CTP, additional MRI may become unnecessary in the diagnostic pathway, and early detection of these small ischemic strokes may influence acute treatment decisions.

Cardiac CTA may be a fast and noninvasive method for depicting cardiac thrombus in the acute stroke phase. It has some advantages over (delayed) echocardiographic imaging and may facilitate in starting anticoagulant treatment in time. Adding cardiac CTA to the standard stroke imaging protocol will cost an additional 2 s, and the additional radiation exposure will be marginal.

Prediction of recurrences has been subject of multiple studies.^25^ However, developed clinical models for long-term prediction have limited discriminative ability with c-statistics not greater than 0.7.^25^ Addition of imaging predictors to clinical models may improve their predictive value.

For this study, we will not exclude particular subgroups of patients with AIS for reasons of clinical applicability and generalizability. We select on acquisition timing as CT findings such as ischemia may differ between patients who present in an early time window when compared with patients who present in a late time window. Different kinds of CT scanners will be used as multiple centers are involved in this study. Although this can lead to heterogeneity of imaging acquisitions, it enables generalization of the results to other stroke centers.

In conclusion, the ENCLOSE study aims to increase the diagnostic accuracy of CTP for detection of small volume infarcts and diagnostic yield of CTA for cardioembolic sources. Besides, the study aims to improve prognostic models for predicting recurrent ischemic stroke. CT-derived predictors, including predictors derived from early cardiac CTA, will be used to improve prognostication of recurrent ischemic stroke.

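### The recurrence model is selected from about 14 candidates on about 60 events, and no internal validation is named, so the reported c-statistic will be too high and the calibration plot will not show overfitting

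*Protocol article*

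**What the plan says.** All references are to the protocol article.

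- **Model derivation** (under Recurrent stroke prediction) starts from a model holding every candidate predictor. It reduces this by backward selection with Akaike's information criterion, fits Cox models and checks proportional hazards on Schoenfeld residual plots. It then says: "The performance of the final model will be evaluated with measures of discrimination and calibration". Discrimination is measured by ROC curves and c-statistics. For calibration: "Calibration will be assessed with calibration plots".
- **Candidate predictors** names seven clinical variables, six imaging variables or groups of variables, and the TOAST subtype.
- **Sample size** (same part) says that "a prediction model containing a maximum of six predictors will be developed for recurrent stroke" and that "at least 60 patients with a recurrent stroke are needed according to statistical guidelines".
- **Abstract and Background** make the added value of CT-derived predictors for recurrence the second goal.
- **Discussion** describes the existing field: "developed clinical models for long-term prediction have limited discriminative ability with c-statistics not greater than 0.7".

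No resampling, shrinkage, split sample or external data set is mentioned anywhere in the article.

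**The concern.** A model that has been selected and fitted in one data set performs better there than in new patients. The gap grows as events per candidate fall and as selection becomes more data-driven. Here the cohort is sized at ten events per predictor for six predictors, but the selection starts from more than twice that number. No events are set aside for testing.

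Two consequences follow if the stated steps are carried out as they stand. First, the c-statistic is biased upward. Second, the calibration plot is drawn where the fitted coefficients are already optimal, so predictions that are too extreme for new patients look correct on average.

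What is at stake is the second goal. An uncorrected c-statistic may look better than those of published clinical models when the model would do no better in new patients. A comparison of a clinical model with a clinical-plus-imaging model is exposed in the same way. Adding predictors cannot lower the maximised likelihood in the same data, and it usually raises the apparent c-statistic.

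**Working it through.** **1. The plan's own sample size.** Inputs from Sample size: six predictors, 60 events, 10% recurrence, 10% loss to follow-up, 90% participation.

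- Events per predictor implied: 60 / 6 = 10.
- Patients with follow-up: 60 / 0.10 = 600.
- Allowing for loss: 600 / 0.90 = 667 (or 600 × 1.10 = 660), against the stated figure of about 650.
- Patients to ask: 650 / 0.90 = 722, against the stated 720.

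The figures reproduce apart from rounding. Forward from 720 asked: 720 × 0.90 × 0.90 × 0.10 = 58.3 events. If 720 are actually included: 720 × 0.90 × 0.10 = 64.8. About 60 events is therefore a fair planning value.

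**2. Events per candidate.** Seven clinical variables + six imaging variables (counting occlusion or stenosis as one, and plaque characteristics as one) + TOAST = 14. If TOAST takes four parameters (an assumption; the coding is not stated), the count is 7 + 6 + 4 = 17.

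- 60 / 14 = 4.3
- 60 / 17 = 3.5

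**3. Why calibration in the same data hides overfitting.** Let ℓ(β) be the Cox partial log-likelihood, with score U(β) and maximum at b, so that U(b) = 0. Refit the model with the linear predictor as the only covariate, with slope s. The derivative of ℓ(sb) with respect to s is b′U(sb), which is zero at s = 1. Because ℓ is concave, the apparent slope is exactly 1 whatever the slope in new patients.

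**4. Size of the optimism.** Cox simulation: 600 patients, 10% events, 14 or 17 candidate parameters, backward elimination by Akaike's criterion with and without a cap of six, 120 replicates per setting. Each selected model was then applied to 15,000 new patients. Predictor effects and prevalences are assumptions: independent predictors, two normal and the rest binary at 30%, with 0, 5 or 6 true effects. Ranges are over the four settings (14 or 17 parameters, cap or no cap).

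| Assumed signal | Apparent c | c in new patients | Excess | Slope in new patients | Apparent c above 0.70 |
|---|---|---|---|---|---|
| None | 0.59-0.60 | 0.50 | 0.09-0.10 | about 0 | 0% |
| Weak | 0.66-0.67 | 0.57-0.58 | 0.08-0.09 | 0.44-0.49 | 12-19% |
| Moderate | 0.71 | 0.64-0.65 | 0.06-0.07 | 0.69-0.70 | 56-67% |
| Strong | 0.78-0.79 | 0.75 | 0.03-0.04 | 0.82-0.87 | 99-100% |

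The apparent slope was 1.0000 in every replicate that kept at least one predictor, as step 3 requires. In the weak and moderate rows the c-statistic in new patients never exceeded 0.70. In the strong row it did so in 97-100% of replicates.

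**5. Does the result depend on selection?** A second simulation used other assumptions (585 followed patients, about 60 events, 400 runs per scenario). With six pre-specified predictors and no selection, apparent c was 0.59 against a true 0.50 with no signal. With modest effects it was 0.66 against 0.61, with a slope of 0.68 in new patients. Backward selection from 14 candidates gave 0.67 against 0.60, with a slope of 0.58. Optimism is present either way.

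**6. Does the remedy work?** In 40 simulated trials of that last scenario, a bootstrap that repeated the selection gave a corrected c of 0.605, against a true 0.600 and an apparent 0.672.

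**The case against.** The strongest objection is that this rests on silence. The article names performance measures. It does not say that they will be computed only in the derivation data or reported uncorrected. It condenses a fuller protocol, and an analysis plan that is not shown may specify resampling. That possibility stands and cannot be excluded. However, the article sets out the sequence in detail, down to how proportional hazards are checked, places the performance evaluation under model derivation, and commits the whole cohort to derivation. Followed as stated, those steps give apparent performance.

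A reader might also infer more than the documents support:

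- **That calibration cannot fail.** The article plans plots and names no calibration slope. A plot in the same data can still show non-linearity, missing interactions or non-proportional hazards. Only overfitting stays hidden.
- **That the evaluation cannot separate a good model from a poor one.** It can, roughly. Apparent c rose from about 0.60 with no signal to about 0.78 with strong signal, and no null replicate passed 0.70. The value is biased, but it is informative.
- **That 0.70 is a success threshold.** It appears once, in the Discussion, as a description of earlier models. No decision rule is attached to it, so the last column of the table is illustrative.

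It is also fair to say that neither simulation measures the added value of imaging directly, and that the optimism is small if the predictors are strong.

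**Conclusion.** The point holds in a limited form. With about 60 events and 14 or more candidate parameters, the described procedure will report a c-statistic that is too high, and its calibration plot will not show overfitting. The excess in c runs from about 0.03-0.04 with strong predictors to about 0.10 with none. The calibration slope in new patients runs from about 0 to 0.87.

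The direction does not depend on the simulation settings. The size does, because predictor effects, prevalences and independence are assumed. The conclusion also assumes that no validation step is specified in a document not shown; if one is, only the article's wording is incomplete. The design and the data collection are unaffected. The weakness lies in what could be claimed about improved prediction and about the added value of CT-derived predictors.

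**What to change.** In Model derivation, add bootstrap internal validation in which every resample repeats the whole procedure: the starting model with all candidates, backward selection, and the final fit. Report the optimism-corrected c-statistic and calibration slope beside the apparent values. Use the corrected values in any comparison with a clinical-only model or with published models, and apply the same correction to both models when added value is assessed. Shrinking the coefficients by the corrected slope is an option, not a requirement.

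The cost is analysis code and a sentence or two of text. No new data are needed. The price is a less favourable reported c-statistic.

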### Ethical considerations

Written informed consent will be acquired from patient or legal representative. The ability of the patient to give informed consent will be evaluated in order to determine whether the patient or the legal representative should be asked for written informed consent. Patients who are incapable of giving informed consent will not be asked to undergo MRI. In case the patient dies before informed consent can be acquired, the patient will be included without obtaining informed consent from his/her legal representative as it is undesirable to burden the legal representative with this request. The ENCLOSE study has been approved by the medical ethics committee of the University Medical Center Utrecht.

## Discussion

CTP has good sensitivity (80%) and specificity (95%) for brain infarct detection.^10^,^11^ However, accurate detection of small volume infarcts is still difficult with CTP because of noise and limited spatial resolution.^38^ In addition, evaluation of the posterior fossa is often hampered by streak artefacts.^39^ In case no stroke is visualized with CT, an MRI is sometimes indicated to ascertain the diagnosis. By improving the detection of small volume stroke by CTP, additional MRI may become unnecessary in the diagnostic pathway, and early detection of these small ischemic strokes may influence acute treatment decisions.

Cardiac CTA may be a fast and noninvasive method for depicting cardiac thrombus in the acute stroke phase. It has some advantages over (delayed) echocardiographic imaging and may facilitate in starting anticoagulant treatment in time. Adding cardiac CTA to the standard stroke imaging protocol will cost an additional 2 s, and the additional radiation exposure will be marginal.

Prediction of recurrences has been subject of multiple studies.^25^ However, developed clinical models for long-term prediction have limited discriminative ability with c-statistics not greater than 0.7.^25^ Addition of imaging predictors to clinical models may improve their predictive value.

For this study, we will not exclude particular subgroups of patients with AIS for reasons of clinical applicability and generalizability. We select on acquisition timing as CT findings such as ischemia may differ between patients who present in an early time window when compared with patients who present in a late time window. Different kinds of CT scanners will be used as multiple centers are involved in this study. Although this can lead to heterogeneity of imaging acquisitions, it enables generalization of the results to other stroke centers.

In conclusion, the ENCLOSE study aims to increase the diagnostic accuracy of CTP for detection of small volume infarcts and diagnostic yield of CTA for cardioembolic sources. Besides, the study aims to improve prognostic models for predicting recurrent ischemic stroke. CT-derived predictors, including predictors derived from early cardiac CTA, will be used to improve prognostication of recurrent ischemic stroke.
